## Abstract

**Background:**

The Ecological Model of Childhood Overweight focuses on characteristics that could affect a child’s weight status in relation to the multiple environments surrounding that child. A community coaching approach allows community groups to identify their own strengths, priorities and identity. Little to no research currently exists related to community-based efforts inclusive of community coaching in creating environmental change to prevent childhood obesity particularly in rural communities.

**Methods:**

A quasi-experimental study will be conducted with low-income, rural communities (*n* = 14) in the North Central region of the United States to mobilize capacity in communities to create and sustain an environment of healthy eating and physical activity to prevent childhood obesity. Two rural communities within seven Midwestern states (IN, KS, MI, OH, ND, SD, WI) will be randomly assigned to serve as an intervention or comparison community. Coalitions will complete assessments of their communities, choose from evidence-based approaches, and implement nutrition and physical activity interventions each year to prevent childhood obesity with emphasis on policy, system or environmental changes over four years. Only intervention coalitions will receive community coaching from a trained coach. Outcomes will be assessed at baseline, annually and project end using previously validated instruments and include coalition self-assessments, parental perceptions regarding the built environment, community, neighborhood, and early childhood environments, self-reflections from coaches and project staff, ripple effect mapping with coalitions and, final interviews of key stakeholders and coaches. A mixed-methods analysis approach will be used to evaluate if Community Coaching enhances community capacity to create and sustain an environment to support healthy eating and physical activity for young children. ANOVA or corresponding non-parametric tests will be used to analyze quantitative data relating to environmental change with significance set at *P* < .05. Dominant emergent themes from the qualitative data will be weaved together with quantitative data to develop a theoretical model representing how communities were impacted by the project.

**Discussion:**

This project will yield data and best practices that could become a model for community development based approaches to preventing childhood obesity in rural communities.

## Background

Approximately one in four preschool age children are considered overweight or obese with higher rates among low-income families [1]. Four years of age appears to be a critical time in overweight and obesity prevention especially among children with a lower socioeconomic status [2]. An obese four-year-old child has a 20 % likelihood of being an overweight adult [3]. Prevention efforts for childhood obesity should be multi-faceted, involving children of all ages throughout all sectors of the environment. Accordingly, the U.S. White House Task Force on Childhood Obesity Report called for multi-sector collaborations to prevent childhood obesity [4].

The Center for Study of Rural America reports that people in rural areas suffer the highest obesity rates in the United States [5]. The geography and infrastructure of rural areas contribute to problems of poor nutrition and physical inactivity among rural populations. Specifically, children living in rural areas in the U.S. are about 25 % more likely to be overweight or obese than their urban counterparts [6]. One theory is that children living in rural areas have fewer chances than urban children for physical activity in their daily routine. While most states have obesity prevention plans, few plans seem to focus on the rural population and their special needs [7].

The Ecological Model of Childhood Overweight focuses on those characteristics that could affect a child’s weight status in relation to the multiple environments surrounding that child [8]. This model examines the combined effects of the community at large, parenting and family factors, and individual factors that impact a child’s weight. The Ecological Model considers the larger community in which the child lives. Consensus is building among researchers that the obesity epidemic is driven by the environment, rather than solely by individual factors [9–13]. Therefore, a closer examination of the community in regard to childhood obesity prevention is warranted.

Experience in community development reinforces the conclusion that work in this aspect must be locally conceived, locally led, and consistent with the cultural identity of the community [14]. A community coaching approach allows community groups to identify their own strengths, priorities and identity. Thus, community coaches may assist communities with an assessment of their strengths and weaknesses, and then engage the community in investigating new ways of solving their problems. Community coaches help the group strategize and gain commitment to move forward and may help groups use the knowledge and understanding they have gained to take their work to a higher level [15]. While information and program ideas are widely available on the internet, information alone does not create change. A community coach could help motivate communities to translate research and information into practice.

To address the issue of childhood obesity in rural communities, a collaborative, multi-state (Indiana, Kansas, Michigan, North Dakota, Ohio, South Dakota, and Wisconsin) effort was formed. Team members include nutrition scientists, community development specialists, and family and youth development specialists from the North Central region of the United States who developed an innovative, integrated research and Extension project. The overall goal of this project is to mobilize capacity in low-income, rural communities to create and sustain an environment and culture of healthy eating and physical activity to prevent childhood obesity in young children.

The specific project objectives are:Existing health related coalitions in 14 rural U.S. communities (two per state, one as an intervention community and one as a comparison community) will be supported to improve the environment for nutrition and physical activity of 4‐year‐old children in their community.The project team will identify or develop community assessment tools and assemble them into a *Child Ecological Model Assessment Tool Kit.*The project team will create a menu of evidence‐based or evidence‐informed educational programs and protocols addressing healthy eating and physical activity for 4‐year‐old children from which communities will select.Community coalitions will create a plan to reduce obesity in their community that is based on the assessment of their community’s environment for 4‐year‐old children.Community coalitions will identify and implement at least one local or institutional policy, system or environmental change that will improve nutrition and one that will increase physical activity for 4‐year‐old children.The project team will assess the perceived value that the community coalition members place on the effectiveness of the menu of evidence‐based or evidence informed educational programs and protocols in improving the environment that sustains healthy eating and promotes physical activity for 4‐year‐old children.The project team will test the main hypothesis that Community Coaching will enhance the capacity of the community in preventing childhood obesity by addressing the needs identified in the assessment and by providing the community coalitions in the intervention community (one per state) with Community Coaches training.

To summarize, existing community health coalitions will assess their environment using an ecological model of childhood overweight and then select evidence-based or evidence-informed approaches to implement over four years to address their community needs. This research will examine the effectiveness of a community coaching model on the ability of a community coalition to address the needs identified to improving the healthy eating and physical activity environment for 4‐year‐old children.

## Methods

### Study design

The focus of this project is to improve understanding of those factors necessary to mobilize communities to make policy, system or environmental changes aimed at the prevention of childhood obesity within seven North Central U.S. States (IN, KS, MI, ND, OH, SD, WI). Using a quasi-experimental design, the research will examine how building community capacity with a community coaching model in rural, low-income communities contributes to the communities’ increased ability to prevent childhood obesity. The Ecological Model of Childhood Overweight will serve as the foundation for reviewing characteristics that could affect a child’s weight status in relation to the multiple environments surrounding that child [8].

Low-income, rural communities will be recruited to apply for the project from each of the seven participating states. Rural areas will be defined based on the Office of Management and Budget’s definition, which delineates an area as rural if there is no presence of a metropolitan statistical area or a core urban area with a population of 50,000 or more [16]. Low-income will be defined based on the community’s average income rate being below the state’s average poverty rate. Other criteria will include that the community has an existing community health coalition and community focus to tackle childhood obesity prevention. Similar-size intervention and comparison communities will be selected from each state. Once selected through an application screening process to ensure that selection criteria are met, communities will be randomly assigned to the intervention or comparison group. Each state will have one intervention and one comparison community. The project sample size (*n* = 14) will be sufficient to detect large effect sizes (d ≥ 0.8) with 95 % power for a two-tailed test at alpha = .05 between intervention and comparison communities from pre to post using the community as the main unit of measure and community level variables as the main outcomes.

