### Statistical analysis

Objectives 1–5 are project development or process objectives which will be evaluated using monthly or annual reports from each state during the five year project. Objective 6 (perceived value of the menu of evidence-based obesity prevention resources) will be evaluated by qualitative data analysis techniques specifically, interviews with community coalition members. The main project objective, objective 7 (enhancement of community capacity to prevent childhood obesity by Community Coaching) will be evaluated using a mixed-methods data analysis approach with data from several of the project instruments (CHLI, Active Where?, and CSAS). Descriptive statistics including frequencies and repeated measures ANOVA or corresponding non-parametric tests will be conducted to detect changes between intervention and comparison communities before and after the four year intervention for quantitative data related to policy, systems and environmental change variables using SAS 9.4 software (SAS Institute Inc.). Significance will be set at *P* < .05.

Qualitative data (reflections and interviews) will be analyzed using the classic analysis approach [23] including constant comparison analysis to generate themes and search for text that inform those themes. Ripple effect mapping will be analyzed through content analysis by categorizing identified community activities and changes into the different levels of the social-ecological model. Dominant emergent themes from the qualitative data will be weaved together with quantitative data to develop a theoretical model representing how communities were impacted by the project.

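### The claimed 95% power for d ≥ 0.8 with 14 communities does not follow from the stated inputs; with d on the analysed scale the design gives about 28% unpaired or 43% paired by state

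*Protocol article*

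**What the plan says.** The objectives in the Background section set the size and layout: "Existing health related coalitions in 14 rural U.S. communities (two per state, one as an intervention community and one as a comparison community"). Study design repeats the allocation ("Each state will have one intervention and one comparison community") and says that communities are assigned at random after screening. That makes seven communities per arm, in seven state pairs.

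The same section says that this number "will be sufficient to detect large effect sizes (d ≥ 0.8) with 95 % power for a two-tailed test". The test is specified as a "two-tailed test at alpha = .05 between intervention and comparison communities from pre to post", and the calculation is made "using the community as the main unit of measure and community level variables as the main outcomes".

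The Statistical analysis section plans that "repeated measures ANOVA or corresponding non-parametric tests will be conducted to detect changes between intervention and comparison communities" before and after the four-year intervention, with significance at P < .05. The article gives no outcome SD, pre-post correlation, within-state correlation or power formula.

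**The concern.** The sentence supplies everything needed for a basic power check: number of units, allocation, effect size, alpha, sidedness, contrast and unit of analysis. Seven units per arm are very few for an effect of 0.8 SD, so 95% power looks implausible on sight.

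This is the only justification of the community sample size in the article, and it supports the main hypothesis on coaching (objective 7). If real power is far below 95%, a non-significant comparison says little about whether coaching has a large effect, while the stated figure could invite the opposite reading.

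**Working it through.** **Inputs (Study design, unless noted).** 14 communities, 7 per arm, one of each per state; d = 0.8, the lower end of the stated range; two-sided alpha .05; community as unit; pre to post. The test is a repeated measures ANOVA (Statistical analysis). With two time points, its group-by-time test is the same as a two-sample t test on community-level change, with 7 + 7 − 2 = 12 df.

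**Trying to reproduce 95% with d on the analysed scale (noncentral t).**

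| Reading | Noncentrality | df | Power |
|---|---|---|---|
| 7 v 7, two-sided | 0.8 × √(7×7/14) = 1.497 | 12 | 0.280 |
| Same, one-sided | 1.497 | 12 | 0.408 |
| Seven state pairs, standardised pair difference 0.8 | 0.8 × √7 = 2.117 | 6 | 0.428 |
| 14 misread as the number per arm | 0.8 × √7 = 2.117 | 26 | 0.531 |
| All 14 as one pre-post group | 0.8 × √14 = 2.993 | 13 | 0.790 |

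The normal approximation for 7 v 7 gives 0.322. The last row has no between-arm contrast, so it is not the stated test, and it still falls short of 95%.

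**With d on the outcome SD, change analysed.** The SD of change is √(2(1 − r)) outcome SDs, so the standardised effect on change is 0.8/√(2(1 − r)), where r is the pre-post correlation. The article does not give r, so a range is shown:

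| r | 0.3 | 0.5 | 0.7 | 0.8 | 0.9 |
|---|---|---|---|---|---|
| Power, 7 v 7 | 0.21 | 0.28 | 0.43 | 0.59 | 0.87 |

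95% power needs a standardised effect of 2.10 on change. Solving 0.8/√(2(1 − r)) = 2.10 gives r ≈ 0.93. Adjusting for baseline instead needs r ≈ 0.92.

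**With d on the outcome SD, state pairs.** The same formula applies, with r now the correlation between the two communities of a pair. Power is 0.43 at 0.5, 0.63 at 0.7, 0.80 at 0.8 and 0.97 at 0.9. 95% needs a standardised pair difference of 1.65. Solving 0.8/√(2(1 − r)) = 1.65 gives r just above 0.88.

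**Repeated-measures routine with Cohen's f.** For two groups and two times, λ = f² × 14 × 2/(1 − r), with 1 and 12 df.

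- f = 0.4, r = 0.5: λ = 0.16 × 28/0.5 = 8.96, power 0.785. Power reaches 95% at r ≈ 0.71.
- A between-arm difference in change of δ outcome SDs corresponds to f = δ/4. So f = 0.4 means δ = 1.6, while δ = 0.8 means f = 0.2.
- f = 0.2, r = 0.5: λ = 0.04 × 28/0.5 = 2.24 = 1.497², which returns the 28% above.

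**What the design can detect, and what 95% would take.**

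| | 80% power | 95% power |
|---|---|---|
| 7 v 7 (SD of the analysed variable) | 1.63 | 2.10 |
| 7 pairs (SD of the pair difference) | 1.27 | 1.65 |

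For d = 0.8 on these scales, 95% power would take 42 communities per arm, or 23 pairs.

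**The case against.** The best defence is that power in a pre-post design depends on the scale of d and on correlations that a condensed article may leave to the full protocol. Much of this stands. The 28% is conditional: it holds if d is on the analysed scale, or if d is on the outcome SD and r = 0.5. A reader might infer that 28% is simply the true power, with a 72% risk of missing a large effect; the document does not fix the scale or the correlation, so that goes too far. Nor is a pre-post correlation near 0.93 the only route to 95%. Similar-size communities are chosen within each state, so pairing is a design feature, and a state-paired analysis gets there with a within-pair correlation just above 0.88.

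The absence of a correlation from the article is not in itself a fault. What remains is that the stated inputs do not give the stated figure, and that the routes to 95% need either a very high correlation or a different effect. A high pre-post correlation would have to hold over a four-year intervention in which both arms are funded to change the environment being measured (Intervention section). The route through f = 0.4 at r ≈ 0.71 might explain how 95% arose, but that is a guess, and it tests a difference in change twice the stated 0.8 SD.

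A further inference would be that the plan intends to read a null result as excluding a large effect. No passage says so. Objective 7 is judged by mixed methods across several instruments, and the Discussion lists limitations. The figure could invite that reading; no more can be claimed.

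**Conclusion.** The concern holds in this form: 95% power for d ≥ 0.8 does not follow from 14 communities, two-tailed alpha .05 and the community as unit. On the analysed scale, power is about 28% unpaired (12 df) and about 43% for seven state pairs. On the outcome SD with change analysed, it is 0.21 to 0.87 for pre-post correlations of 0.3 to 0.9. These figures assume approximate normality and the effect at the lower bound, d = 0.8; larger effects have more power. None of the readings tried yields 95% at d = 0.8 without a very high correlation that the article does not state. The effect is on how the main quantitative comparison is interpreted, since the number of communities is already settled.

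**What to change.** Replace the power sentence in Study design with one that names the SD scale and the assumed correlation. For example: with 7 communities per arm and two-sided alpha .05, power for a standardised difference of 0.8 on the analysed scale is about 28% unpaired, or about 43% for seven state pairs with d on the pair-difference SD; the differences detectable with 80% and 95% power are 1.63 and 2.10 unpaired, and 1.27 and 1.65 paired. If d was meant on the outcome SD, say so and show power over a range of correlations. If the full protocol holds a calculation that gives 95%, state its correlation and formula, and check that its effect size really corresponds to d = 0.8.

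Add one sentence that a non-significant result will not be taken as evidence against a large effect.

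The cost is a sentence or two and a less favourable figure; no communities need adding. The Study status section says that analysis of the main outcomes has yet to begin, so the correction can still be made before results are known.

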### Intervention

Each community will utilize the efforts of a community health coalition to develop a strategic plan and to implement that plan after completing a series of assessments. Communities will be provided with a “menu” of evidence-based or evidence-informed strategies and a set amount of funding each year ($5000) to implement at least one nutrition and one physical activity intervention annually. The menu of evidence‐based or evidence‐informed childhood obesity prevention approaches will be developed by the research team and continually updated and, made available electronically to both intervention and comparison communities. Materials selected will be culturally and ethnically diverse, representing the varied ethnic groups that make up the North Central U.S. region, including Caucasian, Hispanic, Native American, Hmong, and other groups. The menu will include evidence-based nutrition and physical activity curricula, evidence‐based or evidence‐informed strategies as well as recommendations from the U.S. White House Task Force on Childhood Obesity Report to the President [4]. Nutrition interventions will seek to improve the environment within the communities to support an increased intake of fruits and vegetables, increase the variety of vegetables in the diet, or decrease the intakes of foods high in solid fats and added sugars while physical activity interventions will seek to increase the number of children that meet the guidelines for television viewing and computer use, or increased physical activity.

The intervention communities will also be provided with a part-time community coach for the full length of the project. Responsibilities of the coach will be to guide the coalition in identifying, clarifying, and illuminating local childhood obesity issues, goals, prevention strategies, partners and resources. The comparison communities will not be provided with a coach and on their own will choose and implement nutrition and physical activity approaches throughout the duration of the project. A study timeline is provided in Table 1.

**Table 1 Tab1:** Project timeline and milestones

Year	Activities	Milestones
1	• Hire program coordinator	• Staff hired
	• Identify, adapt, and/or develop the Child Ecological Model Assessment Tool Kit	• Tools developed
	• Develop “menu” of selected evidence based or evidence‐informed approaches for improved nutrition and physical activity for 4‐year‐olds	• Communities chosen
	• Choose intervention and comparison communities	
2	• Conduct community assessments	• Child Ecological Model Assessments completed
	• Hire community coaches for intervention communities	• Coaches hired and trained
	• Train community coaches and other key leaders of intervention communities on community coaching	• Interventions implemented
	• Each of the intervention and comparison communities begin implementation of at least one nutrition and one physical activity intervention	
3	• Interventions continue	• Interventions implemented
	• Training continues	• Process evaluations monitor progress of interventions
	• Process evaluations on‐going	
4	• Interventions continue	• Interventions implemented
	• Training continues	• Process evaluations monitor progress of interventions
	• Process evaluations on‐going	
5	• Interventions continue for final year	• Interventions implemented for final year
	• Intervention communities develop sustainability plan	• Data analysis completed and disseminated
	• Complete post‐assessments	• Tool kit and other findings available on‐line
	• Analyze data	
	• Organize findings into a “Best Practices Tool Kit” for dissemination via technology such as eXtension	
	• Research manuscripts and conference proposals begin	

Each state has secured the necessary Institutional Review Board (IRB) approval or exemptions as required by their institution. For the main study intervention where the community was the unit of randomization and intervention, approvals were secured by The Ohio State University Behavioral and Social Sciences IRB and the Michigan State University IRB. Study exemptions were secured by the Kansas State University Research Compliance Office, North Dakota State University IRB, Purdue University Human Research Protection Program IRB, South Dakota State University Office of Research Human Subjects Committee and, University of Wisconsin Extension Human Subjects Protection Committee. When outcomes involved assessment or interviews with human subject participants related to the community interventions, informed written consent was obtained (Ohio State University) or information sheets were provided to participants (North Dakota State University) when required by specific institutional IRB.

